#### MS-nurse consultations

The low-intensity treatment by experienced MS-nurses consists of three consultations of 45 min over a 4-month period. The content of the consultations led by the MS-nurse will cover two important aspects to control for: (1) reliable information on MS-related fatigue; and (2) attention from an experienced MS professional in order to reassure the patient that his/her concerns or questions will be taken seriously [65]. In the first consultation, the patient receives a booklet containing general information about MS-related fatigue and factors that may influence fatigue. This booklet was designed by the TREFAMS-ACE research team to provide patients with standardised information about fatigue, without adding details regarding specific interventions so as to avoid overlap with the trial-specific interventions. In the remaining two consultations, participants will have the opportunity to discuss their personal experiences in coping with fatigue, ask questions about the booklet and discuss other fatigue-related issues. The consultations with the MS-nurses should not be considered as ‘usual care’ because, due to the TREFAMS-ACE study design, the MS-nurses are restricted in referring patients to a psychologist, physiotherapist or other healthcare professional within the hospital. In the Netherlands, timely referral is an important aspect of normal MS-nursing practice.

#### Therapist training

All involved therapists were selected based on their experience with the intervention and with treating MS patients. Furthermore, all received training that was focused on one of the four treatment protocols used in the TREFAMS-ACE study.

Physiotherapists experienced in cardio-respiratory training were introduced to the exercise protocol, the use of the bicycle ergometer, study materials and measurements in TREFAMS-AT.

The psychologists involved in the TREFAMS-CBT study all received an additional 4-day CBT training course at the Expert Centre Chronic Fatigue of UMCN. The training course consisted of an introduction to the protocol, training in the content of each treatment module and how to determine which modules are indicated for a specific participant. The skills needed to change patient cognition and behaviours were practised during role-playing, with the help of simulated patients. To ensure the quality of the CBT, weekly peer conversations between therapists, in which experiences with the TREFAMS-CBT participants will be shared, are part of the therapist training.

Occupational therapists already familiar with energy conservation strategies and the Packer group course ‘Managing Fatigue’ received a 1-day training course in the implementation of the individual Energy Management Course (IECM). This course was given by the researcher, together with an expert therapist in energy conservation management. Training consisted of a thorough explanation of the content of the 12 sessions and how sessions can be individually tailored. In addition, occupational therapists not yet qualified in applying Motivational Interviewing had to attend a 3-day Motivational Interviewing course.

All MS-nurses involved in one of the RCTs participated in a 1-day training course. In this course the MS-nurses shared their approach to taking a fatigue-related nursing history, they were instructed as to how to provide relevant information on MS-related fatigue without giving concrete therapeutic advice, and they were informed of the restrictions concerning the referral of patients to other healthcare professionals within the hospital (MS team members). These newly-learned skills were practised using role-playing.

### Outcome measures

Outcome measures consist of validated self-reported questionnaires, blood and saliva, activity monitoring and physical fitness tests. All primary and secondary outcomes will be assessed 1 week prior to, and at 0, 8, 16, 26 and 52 weeks after randomisation. The self-reported questionnaires will be offered to patients via the internet or on paper, and will be completed at home. Within each self-reported questionnaire, the sequence of questions will be randomised between measurement occasions. The drawing of blood samples (according to the study protocol), physical fitness tests and assessor-based interviews will take place at the outpatient clinic of the participating centres. Saliva sampling will take place at home and includes several time-points per day.

#### Primary outcome measures

1. Fatigue will be measured with the Checklist Individual Strength (CIS20r), domain fatigue [62,66]. This multidimensional questionnaire consists of 20 items, divided into four dimensions of fatigue and related behavioural aspects, including: (a) the subjective experience of fatigue (8 items); (b) reduction in motivation (4 items); (c) reduction of physical activity (3 items); and (d) reduction in concentration (5 items). The CIS20r focuses on fatigue in the past 2 weeks. Each item is answered using a 7-point scale. The CIS20r fatigue score is a sum score that can vary between 8 and 56 points. Recently, the reproducibility, distribution-based responsiveness and concurrent validity of the CIS20r were investigated in patients with MS [67]. Despite good test-retest reliability, a smallest detectable change of 11.8 points was found, leading to the recommendation to monitor trial participants repeatedly over time using a set of complementary fatigue scales [67]. A systematic review of the measurement properties of 31 fatigue questionnaires confirms this recommendation [68].

2. Societal participation will be assessed with the Impact on Participation and Autonomy questionnaire (IPA) [69]. The IPA questionnaire was developed to assess the severity of restrictions in participation and individual needs related to participation and autonomy. The IPA is a generic questionnaire that addresses: (a) perceived participation, reflected in 31 items in five domains, that is, autonomy indoors, autonomy outdoors, family role, social relations, work and education; and (b) the experience of problems related to every aspect of participation, reflected in eight problem experience scores [69]. An anchor-based responsiveness study in a heterogeneous outpatient rehabilitation population showed that the IPA was moderately able to detect within-patient improvement over time [69]. No studies on the responsiveness and minimal important change of the IPA in patients with MS are yet available [70].

#### Secondary outcome measures

MS-related fatigue is a multifaceted symptom with various types of expression. Therefore, several other fatigue measures are also included. The impact of fatigue will be measured with the Modified Fatigue Impact Scale (MFIS) and the Fatigue Severity Scale (FSS) [71,72]. The MFIS assesses the effects of fatigue in terms of physical, cognitive and psychosocial functioning. The FSS evaluates the severity and impact of fatigue in patients with MS. A patient-reported diurnal course of fatigue during 1 day will be assessed using short message services (SMS) technology. Moreover, the Rehabilitation Activities Profile (RAP) and the Medical Outcome Study Short Form 36 (SF36) will be used to measure daily functioning and participation [61,73].

### Determinants

These include descriptive variables, mediators (that is, intervening causal variables), confounding or effect-modifying factors that have been shown to be related to the interventions, and fatigue and participation in MS patients [53,74]. In multifactorial, complex situations such variables can act in different ways in different situations or different analyses and will therefore be further specified in forthcoming articles.

#### Demographic and disease characteristics

Demographic information includes age, gender, ethnicity, living situation, level of education, work and income. The disease-related variables that will be assessed include the type of MS, neurological symptoms, the Expanded Disability Status Scale (EDSS), the number of exacerbations in the year prior to inclusion, the use of disease modifying drugs and other medication, co-morbidities and healthcare use. The EDSS and the Cumulative Illness Rating Scale (CIRS) will be assessed by a physician at baseline and after 52 weeks [75-77]. Cognitive deficits will be assessed at baseline by the Mini Mental State Examination [78].

#### Physical activity and physical fitness

The amount of physical activity and frequency of movement will be registered by means of a tri-axial activity monitor (ActiGraph GT3X+) that will be worn for 7 days. The Physical Activity Scale for Individuals with Physical Disabilities (PASIPD) is a self-reported questionnaire that assesses physical activity over the preceding 7 days. The PASIPD assesses physical activity in three domains: recreation, household and occupation activities [79,80].

In a subgroup of participants, cardio-respiratory fitness will be assessed by means of a maximum capacity test (VO2max test). Participants will perform this test on an electromagnetic bicycle ergometer. Work rate will be progressively increased by 25 + 10 W/min (women) or 25 + 15 W/min (men) until volitional exhaustion, rpm <45 or for safety reasons. In addition, patients will walk as far as possible during a 2-min walk test (2MWT).

#### Cognitive and behavioural factors

Coping style is measured with the Coping Inventory for Stressful Situations (CISS-21) [81,82]. Three main coping styles can be distinguished: task-oriented coping, emotion-oriented coping and avoidance coping. The General Self Efficacy Scale will be used to assess optimistic self-beliefs for coping with a variety of difficult life demands [83]. Possible mood disorders will be assessed with the Hospital Anxiety and Depression Scale (HADS) [55]. The HADS consists of two subscales: depression and anxiety. The tendency to fall asleep during daytime is measured with the Epsworth Sleepiness Scale [84]. Perceptions of fatigue will be measured with the Brief Illness Perception Questionnaire (B-FPQ), which assesses cognitive and emotional representations of fatigue [53]. The B-FPQ is an adaptation of the Brief Illness Perception Questionnaire (B-IPQ), which measures illness perceptions [85]. Fear of progression of MS is measured with the Fear of disease Progression Questionnaire (FoP-Q) [56,57]. Five factors are distinguished: affective reactions, partnership/family, work, loss of autonomy and coping. The Illness Cognitions Questionnaire (ICQ) measures three different generic illness cognitions: helplessness, acceptance and disease benefits [52]. The Social Support List is used to measure the level of social interactions, discrepancies and negative interactions [63].

#### Biological markers

An important part of the TREFAMS research programme concerns the integration and longitudinal study of clinical parameters and biological parameters [38]. HPA-axis functioning will be assessed through the collection and analysis of salivary cortisol. To determine the Cortisol Awakening Response (CAR), saliva will be collected immediately after awakening and after respectively 30 min, 45 min and 60 min post-awakening. Following the fifth sample at 22:00 the participant takes 0.5 mg dexamethasone (low dose dexamethasone suppression test) and saliva is again collected the next morning, immediately after awakening.

Blood will be drawn to determine levels and activity of pro-and anti-inflammatory cytokines [39,86]. Blood and saliva will be collected at the same fixed time-points as for the other outcome measures.

#### Energy saving strategies

To assess which strategies the participants in all three RCTs use to influence their fatigue, we developed the Fatigue Strategies Questionnaire (FSQ). This questionnaire is based on the Energy Conservation Strategies Survey (ECSS) [87] to which we have added a number of strategies on physical activity, cognition and behaviour. Participants will be asked about the strategies they use and how effective these strategies are. To facilitate the meta-analysis of ECM interventions, the participants of the TREFAMS-ECM trial will fill in the original ECSS at 16 weeks [87].

### Sample size

Sample size was calculated based on the CIS20r subscale fatigue. In order to detect a clinically relevant difference of 8 points on the CIS20r subscale fatigue between the study groups in an MS population, with a SD of 12.7, a power of 80%, an alpha of 0.05 and an attrition rate of 20%, 45 patients per group will be needed [47,88]. This amounts to 90 patients for each trial and 270 patients for the entire TREFAMS-ACE programme. Sample size calculation was not adjusted for longitudinal data analyses with repeated measures [89], or for an eventual clustering by care providers or participating centres. Balancing these two factors, we expect that the power of our study will be >80%.

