### Participants

The 270 adult patients (90 patients per RCT, and 45 per intervention group) required will have to fulfill the following inclusion criteria:(a) definitive diagnosis of MS; (b) severely fatigued; (c) ambulatory patients; (d) no evident signs of an exacerbation, or a corticosteroid treatment in the past 3 months; (e) no current infections; (f:) no anaemia; (g) a normal thyroid function. The exclusion criteria are: (a) depression; (b) primary sleep disorders; (c) severe co-morbidity; (d) current pregnancy or having given birth in the past 3 months; (e) pharmacological treatment for fatigue that was started in the past 3 months (for example, Amantadine, Modafinil, Ritalin, Pemoline); (f) non-pharmacological therapies for fatigue that took place in the past 3 months. See Table 1 for the operationalisation of the inclusion and exclusion criteria.

**Table 1 T1:** Inclusion and exclusion criteria TREFAMS-ACE trials

**Inclusion criteria**	**Exclusion criteria**
Definitive diagnosis of MS	Depression (HADS depression >11)
Severely fatigued (CIS20r-fatigue ≥35)	Primary sleep disorders
Aged between 18 and 70 years	Severe co-morbidity (CIRS item scores ≥3)
Ambulatory patients (an EDSS score ≤6)	Current pregnancy or having given birth in the past 3 months
No evident signs of an exacerbation or a corticosteroid treatment in the past 3 months	Pharmacological treatment for fatigue in the past 3 months
No infections (normal leukocytes and C-reactive protein in blood)	Non-pharmacological therapies for fatigue in the past 3 months
No anaemia (normal haemoglobin and haematocrit in blood)	
No thyroid dysfunction (normal thyroid stimulating hormone (TSH) in blood)	

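### The stated inputs require 50 to 52 patients per group, not 45; at 45 the simple comparison has about 75-76% power, so the text does not support the claim of more than 80%

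*Protocol article*

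**What the plan says.** The Sample size section of the protocol article gives the whole calculation in one paragraph. The outcome is fixed first: "Sample size was calculated based on the CIS20r subscale fatigue". The target is set as "In order to detect a clinically relevant difference of 8 points on the CIS20r subscale fatigue between the study groups", "with a SD of 12.7". The result follows: "a power of 80%, an alpha of 0.05 and an attrition rate of 20%, 45 patients per group will be needed". Whether alpha is one- or two-sided is not stated. The section multiplies this up to 90 per trial and 270 for the programme. The Participants section repeats it ("90 patients per RCT, and 45 per intervention group"), and the Abstract gives the same 90 and 270.

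The paragraph then says that the calculation was adjusted neither for repeated measures nor for clustering by care provider or centre. It ends with an overall claim, in per cent: "Balancing these two factors, we expect that the power of our study will be >80".

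Two other sections bear on that claim. Outcome measures schedules follow-up at 8, 16, 26 and 52 weeks. Statistical analyses of the RCTs and meta-analyses plans an intention-to-treat analysis with generalised estimating equations or mixed models over the one-year course.

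**The concern.** All the inputs except sidedness are stated next to the result, so the result can be checked, and it does not follow from them. The group size is too small for the stated attrition, or the stated attrition is about twice what the group size allows for.

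The closing claim inherits the problem. If repeated measures and clustering cancelled exactly, power would stay at the level of the simple calculation. The paragraph treats that level as 80%, but on its own inputs it is about 76%.

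The same sizing is used for all three trials. A trial that finds no difference would be read against a stated power that its own inputs do not give.

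**Working it through.** **Inputs**, all from the Sample size section: difference δ = 8; SD σ = 12.7, so δ/σ = 0.63; α = 0.05; power 80%; attrition 20%; 45 randomised per group. Allocation is 1:1 (Participants). Two-sided α is assumed first.

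**1. Trying to reproduce 45.**

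Evaluable per group, normal approximation:

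n = 2 (1.960 + 0.842)² (12.7/8)² = 39.6, so 40. The noncentral t gives 40.5, so 41.

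| Variant | Evaluable per group | Divided by 0.8 | Multiplied by 1.2 |
|---|---|---|---|
| Two-sided, normal | 40 | 50 | 48 |
| Two-sided, t-test | 41 | 51.25, so 52 | 49.2, so 50 |
| One-sided, normal | 32 | 40 | 38.4, so 39 |

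Dividing by 0.8 is the correct allowance for 20% loss. Multiplying by 1.2 is a common mistake, and it does not give 45 either. No variant returns 45. The correct two-sided figure of 50 to 52 per group would mean 100 to 104 per trial and 300 to 312 in total, against the stated 90 and 270.

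**2. Power at 45 randomised per group.**

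- Evaluable: 45 × 0.8 = 36 per group.
- SE = 12.7 × √(2/36) = 2.993, and 8/2.993 = 2.673.
- Power = Φ(2.673 − 1.960) = Φ(0.713) = 76.2%. The noncentral t gives 75.0%.
- Difference detectable with 80% power: (1.960 + 0.842) × 2.993 = 8.4 points (8.5 by t-test).

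**3. What would make 45 correct.**

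- Attrition of 1 − 40/45 = 11.1% (normal) or 1 − 41/45 = 8.9% (t-test); or
- with 36 evaluable, an SD of about 12.1 or a difference of about 8.4.

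With no attrition, 45 per group gives 84-85%.

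**4. Could the planned model still exceed 80%?** The article gives no correlation or intraclass correlation (ICC), so the values here are assumptions used only to show the range. Take 36 per group with all four follow-ups, equal correlation r = 0.5 between measurements, and the mean of the four follow-ups as the outcome.

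- No baseline adjustment, no clustering: variance factor (1 + 3 × 0.5)/4 = 0.625; SE = 12.7 × √(0.625 × 2/36) = 2.366; power 92%.
- Baseline adjustment, no clustering: factor 0.625 − 0.5² = 0.375; SE = 1.833; power 99%.
- Baseline adjustment, 12 patients per provider, ICC 0.02, provider effect the same at every visit: factor 0.375 + 11 × 0.02 = 0.595; SE = 2.309; power 93%.
- The same with ICC 0.05: factor 0.375 + 11 × 0.05 = 0.925; SE = 2.879; power 79%.

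If clustering inflates only the adjusted variance, the last two become 98% and 94%. A contrast at a single visit would gain less than the four-visit mean.

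**The case against.** The strongest defence is that the simple calculation is not the planned analysis. The section says openly that it adjusted for neither factor, and longitudinal models over four follow-ups can gain a good deal of power. In most of the assumed scenarios above, power is well over 80%. The 36 per group is also a count of completers: patients lost late still contribute earlier visits to a longitudinal model, and the section does not say to which visit the 20% applies. This stands. A reader might infer that none of the three trials has 80% power, or that the trials are too small. The documents do not support either conclusion, because power under the planned model depends on values that the article does not give.

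It can also be said that a condensed article may leave the correlation and ICC to the full protocol or analysis plan. That stands too, and their absence is not the fault here. The fault is that the figures which are printed contradict each other, and no other document can reconcile them without changing one of them.

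The unstated sidedness does not rescue 45. A one-sided 0.05 test would have 84-85% power at 36 per group, but it would call for about 40 randomised.

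Finally, the shortfall is modest: 4 to 5 percentage points of power, or about half a point on the scale. It changes no analysis and no error rate, and a null result should be read from its confidence interval in any case.

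**Conclusion.** The point holds for the simple calculation. On the stated inputs with a two-sided test, 45 per group should be 50 to 52. With 36 evaluable, the two-group comparison has 75.0% (t-test) to 76.2% (normal) power for 8 points. This rests on a two-sided α and on reading 20% attrition as 36 evaluable per group.

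The claim of more than 80% power is unsupported as written, because it is argued from a base that is 4 to 5 points lower than the paragraph states. It is not shown to be false: the net gain from repeated measures over clustering must now close that gap, and it may well do so.

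**What to change.** Make the sample-size sentence agree with itself, in one of two ways:

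- *45 randomised per group, 36 expected after 20% attrition, gives about 75% power (two-sided alpha 0.05) for 8 points, before any gain from repeated measures or loss from clustering*; or
- keep 80% power and state the attrition that 45 per group can absorb, about 10%.

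State the sidedness of alpha in either case. Keep the claim of more than 80% only if it is recomputed from the corrected base under the planned longitudinal model, with the assumed within-patient correlation and ICC given beside it. Otherwise delete it.

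The cost is wording, and the stated power becomes slightly less favourable. No extra patients are needed, and recruitment, already under way according to Trials' status, is not affected.

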### Randomisation

Patients eligible for participation in the study will be randomised to either the trial-specific intervention or the consultations with the MS-nurse after the baseline measurements have been completed. The randomisation scheme is computer-generated with random variable block sizes. An independent investigator within each main study centre will need to login to the web-based randomisation facility to carry out the randomisation, and will inform the patient and the therapist as to the therapy allocation.

### Blinding

The assessors responsible for physical fitness tests and interviewer-based measures will be told in which week patients need to be measured but will not know which treatment patients receive. Patients will be instructed not to disclose which treatment they are receiving. Furthermore, the analyses of blood and salivary in the clinical chemistry laboratory, and the statistical analyses of the between-group differences, will be performed by research staff blinded to the treatment allocation of the participants.

### Serious adverse events

Based on previous research, AT, CBT, ECM and consulting the MS-nurse are expected to be safe treatment methods in patients with MS [16-21,23-26,90,91]. However, all therapists and assessors involved in the studies will be instructed to report all serious adverse events (SAE) to the principal investigators, after which they will be reported to the Medical Ethical Committee. An SAE is any untoward medical occurrence in a participant that is not necessarily associated with the treatment, but that is lethal, and/or threatens the life of the participant, and/or requires hospitalisation or prolongation of existing hospitalisation, and/or causes persistent or significant disability or incapacity.

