**Methods/Design:**

Ambulatory patients (*n* = 270) suffering from MS-related fatigue will be recruited to three single-blinded randomised clinical trials (RCTs). In each RCT, 90 patients will be randomly allocated to the trial-specific intervention or to a low-intensity intervention that is the same for all RCTs. This low-intensity intervention consists of three individual consultations with a specialised MS-nurse. The trial-specific interventions are Aerobic Training, Cognitive Behavioural Therapy, and Energy Conservation Management. These interventions consist of 12 individual therapist-supervised sessions with additional intervention-specific home exercises. The therapy period lasts 16 weeks. All RCTs have the same design and the same primary outcome measures: fatigue - measured with the Checklist Individual Strength, and participation - measured with the Impact on Participation and Autonomy questionnaire. Outcomes will be assessed 1 week prior to, and at 0, 8, 16, 26 and 52 weeks after randomisation. The assessors will be blinded to allocation. Pro- and anti-inflammatory cytokines in serum, salivary cortisol, physical fitness, physical activity, coping, self-efficacy, illness cognitions and other determinants will be longitudinally measured in order to study the neurobiological mechanisms of action.

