## Methods/Design

### Design

TREFAMS-ACE is a multicentre programme that includes three single-blinded RCTs with repeated measurements in time, in which the effectiveness of Aerobic Training, CBT and Energy Conservation Management on MS-related fatigue and participation in patients with MS will be investigated. All RCTs will use the same two-parallel-arms design (Figure 1), the only difference being the specific intervention applied [28]. Patients will be randomised to receive either a high-intensity trial-specific treatment, which consists of a series of 12 therapist-led sessions in 4 months, or a low-intensity treatment by an experienced MS-nurse, which consists of three consultations in 4 months. Participants will be followed for 1 year.

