### Interventions

#### Aerobic training (AT)

AT aims to improve the participant’s fitness and consists of 12 physiotherapist-led exercise sessions on a bicycle ergometer (Table 2). Moreover, participants will be provided with an identical bicycle ergometer at home on which they will be asked to perform additional training sessions, leading to the recommended three sessions per week. Each 30-min interval-type training session consists of six cycles of 5 min. Each cycle consists of 3 min of low intensity exercise, 1 min of moderate intensity exercise and 1 min of high intensity exercise. At the start of the treatment and after 8 weeks of training, current fitness levels will be assessed with a graded maximal exercise test to volitional exhaustion. Following the 8-week maximal exercise test, exercise intensities will be adjusted to meet the newly obtained fitness level. After completion of the supervised training programme, patients will be encouraged to continue exercising and to remain physically active. Generally, physiological adaptations to aerobic training occur when: (1) the training intensity is at least 60% VO2max, and (2) the training is carried out at least three times a week [40]. The current treatment protocol addresses both factors.

**Table 2 T2:** AT programme

**45-min session of bicycle ergometer training**	**Details**
Warming-up	• 5 min at 25% to 40% Wmax
Aerobic training	• Six cycles of 5 min: 3 min 40% Wmax, 1 min 60% Wmax and 1 min 80% Wmax
	• Cadence: 60-80 revolutions per min (rpm)
	• Heart rate should not exceed 80% of the predicted maximal heart rate
	• Training intensity will be updated once during the training, according to the 8-week maximal exercise test
	• The work rate can be adjusted, based on the clinical expertise of the supervising physiotherapist
Cooling down	10 min
	• All training sessions and adjustments to the work rate are recorded in the training log
Home exercises	Participants will be provided with an identical bicycle ergometer at home so that they can perform additional training sessions, leading to the recommended three sessions per week

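### No serious adverse event enquiry identical in both arms is described, so with 12 therapist sessions against 3 nurse consultations passive reporting can capture events unequally during weeks 0-16.

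*Protocol article*

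**What the plan says.** The Serious adverse events section of the protocol article gives one reporting route: "all therapists and assessors involved in the studies will be instructed to report all serious adverse events (SAE) to the principal investigators", who pass the reports to the ethics committee. The definition does not depend on attribution: "An SAE is any untoward medical occurrence in a participant that is not necessarily associated with the treatment". The section describes no scheduled question to patients and does not say that the route is exclusive.

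The Design section makes contact unequal on purpose. One arm receives "a high-intensity trial-specific treatment, which consists of a series of 12 therapist-led sessions in 4 months", the other "a low-intensity treatment by an experienced MS-nurse, which consists of three consultations in 4 months". The abstract adds: "The therapy period lasts 16 weeks". The nurses count among the therapists, since the Therapist training section says that "all received training that was focused on one of the four treatment protocols used in the TREFAMS-ACE study", and the nurse protocol is the fourth.

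Assessments are scheduled alike in both arms, at weeks 8, 16, 26 and 52 after the week-0 measurement (Outcome measures). Self-report questionnaires are completed at home. Interviews, fitness tests and blood sampling take place in the outpatient clinic.

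The Blinding section keeps assessors unaware of allocation and adds: "Patients will be instructed not to disclose which treatment they are receiving". For the period after treatment, the Aerobic training section states: "After completion of the supervised training programme, patients will be encouraged to continue exercising and to remain physically active".

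**The concern.** An instruction to report is not an instruction to ask. If staff pass on only what patients happen to mention, the number of events recorded depends on how often patients meet a reporter. Here that frequency is part of the treatment contrast, so it differs by arm throughout the therapy period.

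The likely direction is against the trial-specific treatments: the same true event rate would give more recorded events in the arm that is seen more often. All three trials share the design, so pooling them would not remove the effect. The article expects all four treatments to be safe and intends the results to inform clinical guidelines, so any by-arm table of SAEs should reflect events rather than contact.

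After week 16 no therapist contact is scheduled, and of the named reporters only the assessors remain, at weeks 26 and 52. Events in that period may come to light late or not at all, in either arm.

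**Working it through.** The article gives no figure to reproduce here. The check counts scheduled contacts and then illustrates what the difference could mean.

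**Inputs from the article.** Therapist contacts: 12 versus 3 over 16 weeks (Design; abstract). Assessor contacts: weeks 8, 16, 26 and 52 in both arms (Outcome measures).

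**Scheduled contacts with named reporters, trial-specific arm versus nurse arm**

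| Period | Therapist | Assessor | Total | Ratio |
|---|---|---|---|---|
| Weeks 0-16 | 12 vs 3 | 2 vs 2 | 14 vs 5 | 2.8 |
| After week 16 | 0 vs 0 | 2 vs 2 | 2 vs 2 | 1.0 |
| Weeks 0-52 | 12 vs 3 | 4 vs 4 | 16 vs 7 | 2.3 |

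**Illustration.** Assumptions, none of them from the article:
- therapist sessions are evenly spaced over weeks 0-16;
- every patient meets an assessor at all four time-points;
- an event is equally likely at any moment of the period considered;
- each later contact reveals it independently with probability p.

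An event followed by k contacts up to week 52 is captured with probability 1 − (1 − p)^k. Capture for the period is the average of this over event times.

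*Nurse arm, events in weeks 0-16.* Consultations fall at weeks 5.33, 10.67 and 16. For events before week 5.33, k = 7 (1/3 of the period); from 5.33 to 8, k = 6 (1/6); from 8 to 10.67, k = 5 (1/6); from 10.67 to 16, k = 4 (1/3). At p = 0.1 capture is 1 − [0.9^7/3 + 0.9^6/6 + 0.9^5/6 + 0.9^4/3] = 1 − [0.1594 + 0.0886 + 0.0984 + 0.2187] = 43.5%.

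*Trial-specific arm, events in weeks 0-16.* Sessions fall every 1.33 weeks, which gives twelve equal intervals with k = 16, 15, 14, 13, 12, 11 before week 8 and k = 9, 8, 7, 6, 5, 4 after it. At p = 0.1 the average of 1 − 0.9^k over these is 62.1%.

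*Either arm, events after week 16.* k = 2 for weeks 16-26 (10/36 of the period) and k = 1 for weeks 26-52 (26/36). At p = 0.1: (10/36)(0.19) + (26/36)(0.10) = 12.5%.

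| Assumed p | Weeks 0-16, trial-specific | Weeks 0-16, nurse | Difference (points) | After week 16, either arm |
|---|---|---|---|---|
| 0.1 | 62.1% | 43.5% | 18.6 | 12.5% |
| 0.3 | 93.6% | 84.5% | 9.1 | 35.8% |
| 0.5 | 99.0% | 96.9% | 2.1 | 56.9% |
| 0.7 | 99.9% | 99.7% | 0.2 | 75.8% |
| 0.9 | >99.9% | >99.9% | <0.1 | 92.5% |

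The imbalance is confined to weeks 0-16 and matters mainly when p is low. After week 16 the arms are equal. There the issue is delay: the longest gap between scheduled contacts is 52 − 26 = 26 weeks.

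**The case against.** The strongest reply is that this is a journal article. Collection forms and enquiry procedures may sit in a full protocol that is not shown, and nothing in the SAE section is false. SAEs are also conspicuous by definition (death, threat to life, hospitalisation, lasting disability), so a low p needs a reason, and from p = 0.5 upward the imbalance is about 2 points or less. Finally, the article describes no by-arm SAE comparison. The first two arguments limit the size of the problem. They do not remove it, because the article does state a route, that route is combined with deliberately unequal contact, and no section shown equalises enquiry. The third means that the harm arises only when events are tabulated by arm.

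Four stronger readings are tempting and not supported.

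- *Therapists and assessors are the only source.* The article does not say so. Co-morbidities and healthcare use are also recorded, and a physician assesses patients at week 52 (Demographic and disease characteristics), although none of this is linked to SAE reporting and the timing of healthcare use is not given.
- *Detection differs fourfold.* The 12 to 3 ratio omits the equal assessor contacts, and a ratio of contacts is not a ratio of detection probabilities, as the table shows.
- *Patients must hide events from assessors.* The Blinding section bars disclosure of treatment, not of events, and an admission can be reported without naming the allocation. What remains is narrower: the article does not say how to report an event that is hard to describe without revealing treatment.
- *About 9 patients per arm (20% of 45) escape observation.* The 20% is a sample-size allowance for attrition. It does not say when patients leave or whether those who stop therapy also stop assessments.

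**Conclusion.** The point holds in limited form. As described, SAE ascertainment has no scheduled component common to both arms, and during weeks 0-16 patients in the trial-specific arm have 14 scheduled contacts with named reporters against 5. If reporting is passive, by-arm counts for that period are not fully comparable, with more events likely to be recorded in the trial-specific arm.

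The illustrated difference runs from about 19 points of capture at p = 0.1 to well under 1 point at p = 0.7 or more. The article gives no basis for choosing p, and the figures also rest on the assumed session spacing and on independence between contacts. After week 16 the arms are observed equally, so late or missed events there reduce completeness without creating imbalance. The change is worth making because it is cheap; the point does not touch the efficacy analyses.

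**What to change.** - Add one identical item on SAE-defining events (such as hospital admission or new lasting disability, with dates) to the existing self-report questionnaire at weeks 8, 16, 26 and 52 in both arms. Include patients who stopped treatment but remain in follow-up.
- Have the answers read by unblinded study staff rather than the blinded assessors.
- State in the Blinding section that the non-disclosure instruction does not restrict reporting an event to those staff.
- Base any by-arm SAE comparison on these symmetric reports, and list spontaneous therapist reports separately.

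The cost is a slightly longer questionnaire, more reports to read, and a duty for unblinded staff that the article does not yet assign. No extra visits are needed. Two limits remain. The item equalises enquiry but does not shorten the gap between weeks 26 and 52, and it cannot reach patients lost to follow-up. It also comes too late for time-points already passed by the 104 patients randomised at manuscript submission; the other 270 − 104 = 166 planned patients could be covered throughout only if the item were in place before they entered.
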